### 5 Number of Participants

Indicate the total number of participants to be recruited and enrolled

- Provide a rationale for the proposed enrollment number
- What percentage of screened individuals will likely qualify for the study?

**We will screen ~300 obese Latino youth for prediabetes and anticipate that 120 will meet eligibility into the trial. These estimates are based on rates of elevated 2-hour glucose in our current study (~40% exhibit 2-hour glucose  $\geq 120$  mg/dl).**

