**Specific Aim 4:** To examine the cost effectiveness of the intervention, we will estimate the incremental cost-effectiveness ratio (ICER) of the intervention compared to UCC based on changes in 2-hour glucose. The cost effectiveness analyses will be conducted from the societal perspective using 2-hour glucose at 12 months, direct medical costs, and non-medical costs. Direct medical costs include: personnel, intervention materials, MD and RD visits, lab tests, and procedures. The non-medical costs will be participant time for travel, productivity loss, and commercial services for PA and nutrition. Base case and sensitivity analyses will be conducted using TreeAge software. The base case analysis model will use 6-month intervention costs and glucose tolerance at 12-months. ICERs will be calculated by dividing incremental costs by incremental effectiveness (change in 2-hour glucose). The results will indicate whether improved glucose tolerance leads to cost savings. Costs collected throughout the study will be inflated based on the published inflation rates in US dollars at the end of the study.

Confidentiality will be protected through the use of study identification numbers that will be kept separate from personal identifiers. A secure, password protected database will serve as the link between study IDs and source documents which will be kept in separate double-locked file cabinets at Arizona State University in the Southwest Interdisciplinary Research Center (SIRC) data storage in the UCENT building room 700. With the exception of the consent, contact information sheet, eligibility, clearance forms, and lab reports used in the context of the lifestyle class, all study materials will identify participants solely by the assigned code numbers. Blood specimens will be stored with ID numbers in the PI's freezer in ABC-1 rm 259-A. Members of the research team will have access to de-identified data. ID numbers will be used and de-identified data will be entered into a password protected computerized database after baseline testing and confirmation of eligibility. Data will be stored for 7 years; paper documents will be shredded and electronic files will be erased.

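### Aim 4's dollars-per-mg/dl ratio cannot show cost savings from the costs listed, and no method is given for its sampling uncertainty

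*Supplement*

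**What the plan says.** Aim 4 (protocol section 2) is to estimate the incremental cost effectiveness of the programme for improving glucose tolerance. Section 8 describes this as an initial examination. The method is in section 16, under Specific Aim 4:

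- **Summary measure:** "ICERs will be calculated by dividing incremental costs by incremental effectiveness (change in 2-hour glucose".
- **Horizon:** "The base case analysis model will use 6-month intervention costs and glucose tolerance at 12-months".
- **Costs:** the perspective is societal. "Direct medical costs include: personnel, intervention materials, MD and RD visits, lab tests, and procedures". Non-medical costs are participants' travel time, lost productivity, and commercial activity and nutrition services.
- **Uncertainty:** "Base case and sensitivity analyses will be conducted using TreeAge software". The text does not say what is varied, over what range or with what distribution.
- **Conclusion to be drawn:** "The results will indicate whether improved glucose tolerance leads to cost savings".

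On size, section 5 says "We will screen ~300 obese Latino youth for prediabetes" and "anticipate that 120 will meet eligibility into the trial". The documents give no effect size, SD of 2-hour glucose, cost figure, allocation ratio, expected dropout rate or value placed on a 1 mg/dl reduction.

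**The concern.** There are two separate problems.

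The first is what the ratio is asked to show. Whether the programme saves money depends on the incremental cost alone. Dividing that by a glucose difference gives a price per mg/dl and discards the sign needed to answer the question. In addition, none of the listed costs is described as a cost that falls because glucose tolerance has improved.

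The second is precision. The ratio's denominator is an estimated difference in 2-hour glucose. If that difference is small relative to its standard error, the ratio has no finite confidence interval and may take the wrong sign. The plan names no method that would reveal this.

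At stake is a published dollars-per-mg/dl figure that looks firmer than the data allow, attached to a statement about savings that the analysis cannot support.

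**Working it through.** **1. The plan's own figure.** The approximate number screened is 300 and the yield is about 40% (section 5). 300 × 0.40 = 120, which reproduces the planned number. It is a recruitment yield, not a precision or power calculation.

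**2. What the ratio shows.** Let ΔC be the incremental cost and ΔE the incremental reduction in 2-hour glucose, so ICER = ΔC/ΔE. The programme saves money if and only if ΔC < 0. With illustrative values, +$2,000/+10 mg/dl and −$2,000/−10 mg/dl both give $200 per mg/dl; the first is dearer and better, the second cheaper and worse. Section 8 defines improvement as a decrease, while the denominator in section 16 is a change with no stated direction. If change is taken as follow-up minus baseline, a dearer and effective programme gives +$2,000/−10 = −$200, which could be misread as a saving. A sign convention is needed.

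**3. Whether the listed costs can carry a saving from better glucose tolerance.**

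| Listed item | Fall attributed to better glucose tolerance? |
|---|---|
| Personnel, materials | No; delivery cost |
| Physician and dietitian visits, tests, procedures | None described |
| Travel time, productivity, commercial services | None described |
| Avoided diabetes care | Not listed |

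Usual care includes physician and dietitian visits (section 8), so ΔC could in principle be offset by those. Such an offset would come from replacing visits, not from improved glucose tolerance. This step needs no assumed SD, effect or sample size.

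**4. Stability of the ratio.** Assumptions, none from the documents: 1:1 allocation, 60 per arm, normal approximation, no clustering, effect d in units of the (residual) SD of 2-hour glucose, 95% intervals.

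- SE = √(1/60 + 1/60) = 0.183 SD.
- A 95% Fieller interval is bounded only if the observed difference exceeds 1.96 × 0.183 = 0.36 SD.
- P(unbounded) = Φ(1.96 − d/SE) − Φ(−1.96 − d/SE).
- P(wrong-sign denominator) = Φ(−d/SE).

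At d = 0.2, d/SE = 1.095, so P(unbounded) = Φ(0.865) − Φ(−3.055) = 0.81. The other rows follow in the same way. The last two columns allow for 20% loss (N = 96) and for 2:1 allocation.

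| d | Unbounded, 60 per arm | Wrong sign, 60 per arm | Unbounded, 48 per arm | Unbounded, 80:40 |
|---|---|---|---|---|
| 0.2 | 81% | 13.7% | 83% | 82% |
| 0.4 | 41% | 1.4% | 50% | 46% |
| 0.5 | 22% | 0.3% | 31% | 27% |
| 0.6 | 9% | 0.05% | 16% | 13% |
| 0.8 | 0.8% | <0.01% | 2.5% | 1.5% |

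For orientation, the effect detectable with 80% power at 60 per arm is (1.96 + 0.84) × 0.183 = 0.51 SD.

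**5. In dollars (illustration only).** Assume an SD of 20 mg/dl, ΔC = $2,000 and a cost SD of $1,000, with costs and effects drawn independently (400,000 draws). At 0.2 SD the true ICER is 2,000/4 = $500 per mg/dl, with a 95% sampling range of −$4,507 to $5,162. At 0.6 SD it is 2,000/12 = $167, with a range of $100 to $416.

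**The case against.** The other side has several fair points.

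- **Sensitivity analyses are planned.** A reader might infer that Aim 4 reports a bare ratio with uncertainty ignored. The text does not support that: it names sensitivity analyses and speaks of ICERs in the plural. What can be said is that their content is unspecified and nothing shows that they cover sampling error.
- **This is an ethics-board form with no separate analysis plan shown.** The bootstrap scheme and the choice of plots could be left to such a plan, so their absence alone would be a weak point. But the form asks for the analysis plan in section 16, which does fix the ratio, the base case and the conclusion to be drawn. Following that text leads to an unsupported statement.
- **The denominator is analysed elsewhere.** Aim 1 gives a baseline-adjusted comparison of 2-hour glucose at 12 months, and an analyst sees numerator and denominator before dividing. That limits the risk of misreading a negative ratio. It gives no uncertainty for the cost difference or for the pair jointly.
- **Instability is assumed, not shown.** A reader might infer that about 120 youth is by itself too few for a usable ICER. The documents give no effect size or SD, and the problem largely fades from about 0.6 SD upward.
- **The plan does not promise savings.** It says only that the results will indicate whether they occur. That is correct, but the analysis cannot settle that question either.

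**Conclusion.** The point holds in two parts of unequal weight. The firmer part is structural: a dollars-per-mg/dl ratio built on 6-month intervention costs, with no avoided diabetes care listed, cannot indicate whether improved glucose tolerance saves money. A larger trial would not change that, so it should not be read as a sample-size problem.

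The second part is conditional. No method for the sampling uncertainty of the ratio is specified. Assuming 60 per arm, the chance of an unbounded 95% interval runs from about 81% (0.2 SD) through 22% (0.5 SD) to 9% (0.6 SD) and under 1% (0.8 SD). These figures depend on assumptions about effect and allocation that the documents do not settle.

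Aim 4 is a named specific aim but not the primary one. The plan should be changed; the primary efficacy result is unaffected.

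**What to change.** In section 16, Specific Aim 4:

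1. Report incremental cost and incremental 2-hour glucose **reduction** separately, each with a 95% interval, and state the sign convention. Read any saving from the incremental cost and its interval.
2. Give the joint uncertainty by a participant-level bootstrap of cost and effect pairs where participant-level costs exist, with shared programme costs (personnel, materials) varied probabilistically. State what the sensitivity analyses vary and over what ranges.
3. Present the cost-effectiveness plane, and net benefit, λ × ΔE − ΔC, or an acceptability curve over a range of λ in dollars per mg/dl.
4. Replace the savings sentence with one saying that the results will estimate the cost per mg/dl reduction in 2-hour glucose and its uncertainty.
5. Note clustering by class as a limitation. With groups of 8–10, 60 intervention youth make 60/10 = 6 to 60/8 = 7.5 classes, which is too few for a bootstrap of whole classes to be reliable, so it should not be required.

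The cost is a little more analysis and a result that looks less precise. The protocol describes no instrument for participant-level costs, so the team should confirm what was collected before committing to step 2.

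### The Aim 4 base case yields a cost per mg/dl of 2-hour glucose; it cannot show that improved glucose tolerance saves money, as the plan says it will

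*Supplement*

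**What the plan says.** Everything specific to the cost analysis is in Section 16, Specific Aim 4.

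- **Perspective:** "The cost effectiveness analyses will be conducted from the societal perspective using 2-hour glucose at 12 months, direct medical costs, and non-medical costs".
- **Medical cost list:** "Direct medical costs include: personnel, intervention materials, MD and RD visits, lab tests, and procedures".
- **Non-medical costs:** "The non-medical costs will be participant time for travel, productivity loss, and commercial services for PA and nutrition".
- **Base case:** "The base case analysis model will use 6-month intervention costs and glucose tolerance at 12-months".
- **Ratio:** incremental cost divided by incremental effectiveness, where effectiveness is the change in 2-hour glucose.
- **Further analyses:** "Base case and sensitivity analyses will be conducted using TreeAge software". Their content is not given.
- **Period of cost collection:** "Costs collected throughout the study will be inflated based on the published inflation rates in US dollars at the end of the study".
- **Conclusion to be drawn:** "The results will indicate whether improved glucose tolerance leads to cost savings".

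Section 2 states Aim 4 only as estimating incremental cost-effectiveness between the groups. The design paragraph of Section 8 calls the analysis initial. Neither mentions savings.

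**The concern.** A cost-effectiveness ratio answers the question of what one unit of effect costs. Whether the effect itself lowers spending is a different question. Answering it needs a cost that could fall because glucose is better, such as later clinic visits, medicines or hospital care, or else a model that converts a glucose change into later cost. The plan promises an answer to the second question while its base case describes only the first.

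What is at stake is the conclusion drawn from Aim 4. If the intervention arm proves dearer to run, the sentence invites a report that better glucose tolerance does not save money. If it proves cheaper, it invites the opposite report. The base case would have tested neither statement.

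**Working it through.** The documents give no cost, no ratio and no expected effect for Aim 4, so there is no figure to reproduce. The check compares what goes into the ratio with the conclusion drawn from it.

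**1. The two windows.** The base-case numerator is six months of intervention costs. The denominator uses glucose at 12 months. Section 8 (Booster Sessions) places three sessions in months 7, 8 and 9. These are part of the programme and come before the 12-month measurement, but they fall outside a six-month cost window. Section 9 counts 72 intervention sessions, which 20 education sessions plus two activity classes a week for 26 weeks reproduces: 20 + 2 × 26 = 72. Adding the boosters gives 75, so the window leaves out 3/75 = 4% of programme sessions by count. The effect is credited to all of them.

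**2. What drives the numerator.** The intervention arm is scheduled for 72 sessions in the first six months. Under Usual Care Control, Section 8 schedules two endocrinologist and two dietitian contacts, at baseline and 6 months: 2 + 2 = 4. The base-case cost difference therefore mainly reflects the volume and unit price of delivery, and a positive difference is to be expected from the design.

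**3. What a larger effect does to the ratio.** Write ΔC for incremental cost and ΔE for the reduction in 2-hour glucose relative to usual care, so that ICER = ΔC/ΔE. Take ΔC as delivery cost, as in the base case. All values here are assumptions.

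| Assumed ΔC (USD per youth) | ΔE = 2 mg/dl | ΔE = 5 | ΔE = 10 | ΔE = 20 |
|---|---|---|---|---|
| 500 | 250 | 100 | 50 | 25 |
| 1,500 | 750 | 300 | 150 | 75 |
| 3,000 | 1,500 | 600 | 300 | 150 |

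Entries are USD per mg/dl. A larger effect lowers the price per mg/dl. At no point does it turn into a saving.

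**4. What a savings conclusion would need.** Let s be the later cost avoided per mg/dl of improvement. Net cost is ΔC − s × ΔE, and better glucose saves money on balance only if s × ΔE exceeds ΔC. The plan describes nothing that estimates s: no downstream cost is named, no horizon beyond 12 months is set, and no relation between glucose and cost is specified.

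**The case against.** The strongest reply is that the cost lists are wider than trial delivery. The direct list opens with a word that leaves it incomplete, and its physician and dietitian visits, tests and procedures are not restricted to protocol visits. Productivity loss need not come from attending classes, and commercial activity and nutrition services most naturally mean what families buy elsewhere. Costs are collected throughout the study, and sensitivity analyses are planned. Glucose may also change well before month 12: the programme runs to month 6 and Aim 1 tests a 6-month effect, so some offset could fall inside the cost window.

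All of that stands, and it rules out a stronger reading. A reader might infer that every listed cost is one of delivering or attending the two arms, and hence that incremental cost could not respond to glucose under any analysis. The documents do not support this. Nor do they say that the sign of the ratio will be read as savings or no savings; that sign depends on both numerator and denominator, and on how a fall in glucose is coded.

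It is also fair that no separate analysis plan is shown. Detailed cost definitions, resource-use forms and sensitivity scenarios are often left to such a document, so their absence here is not the fault.

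None of this makes the savings sentence follow. The base case is the only analysis whose content is described, and it is limited to six-month intervention costs. An unnamed sensitivity analysis does not supply a link from glucose to cost. Even a full 12-month comparison of costs between arms would estimate the effect of assignment by all routes; it would not by itself attribute a saving to glucose.

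**Conclusion.** The concern holds for the base case and the sentence that concludes from it. As described, the base case supports an incremental cost per mg/dl and does not support a statement that improved glucose tolerance saves money. The mismatch between the six-month cost window and the 12-month effect adds a smaller problem: the three booster sessions count towards the effect but not the cost.

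The consequence is limited. One sentence in one aim claims too much. The ratio can still be calculated, Aim 4 as worded in Section 2 is still met, and Aims 1 to 3 are untouched. No dollar size can be attached, because the documents contain no prices; the table above rests on assumed values and shows only how the ratio behaves. The verdict assumes that the base case is the main result and that intervention costs means the cost of providing the programme and its comparator.

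**What to change.** Replace the savings sentence in Section 16, Specific Aim 4, with:

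> The results will give the incremental cost of the intervention per mg/dl reduction in 2-hour glucose at 12 months; they do not estimate savings from improved glucose tolerance.

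This costs nothing beyond giving up an unsupported claim, and it brings the section into line with the aim in Section 2.

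If the savings question is to be kept, count costs in both arms over the full 12 months. Include the booster sessions and health-care use outside the study, collected in the same way in each arm, and report delivery cost and other health-care cost separately. Word the resulting conclusion as a between-arm cost difference unless a model linking glucose to cost is also specified. This optional route would need a short resource-use questionnaire, which could be given at the 6- and 12-month testing visits already planned.

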### 17 Safety Monitoring

This is required when research involves more than Minimal Risk to participants. The plan might include establishing a data monitoring committee and a plan for reporting data monitoring committee findings to the IRB and the sponsor. Describe:

- The plan to periodically evaluate the data collected regarding both harms and benefits to determine whether participants remain safe.
- What data are reviewed, including safety data, untoward events, and efficacy data?
- How the safety information will be collected (e.g., with case report forms, at study visits, by telephone calls with participants).
- Who will review the data?

## BIOSCIENCE INSTRUCTIONS AND TEMPLATE

NUMBER

HRP-503b

DATE

3/22/2022

PAGE

12 of 13

In compliance with the National Institutes of Health policy for protection of human subjects in clinical studies, we will implement the following Data Safety Monitoring Board (DSMB) policy. This DSMB policy serves to protect the health and safety of human subjects and provide information relevant to subjects' continuation in clinical studies. The DSMB will include the Chair ([name]), the Associate Dean of Research in the College of Nursing ([name]), a statistician, and senior investigators. This DSMB will meet quarterly to review progress pursuant to presentation of a summary report from [name] by ensuring that policies on the identification and reporting of adverse events to the appropriate regulatory bodies, which can include the ASU institutional review board and the project officer at the National Institutes of Health, have been implemented diligently and promptly. Prompt and due diligence in reporting of adverse events (i.e., within 24 hours during the week and on the next working day following a weekend) to the regulatory bodies will remain the express duty of the PI. At baseline and every 4 weeks during data collection, we will examine the results for evidence of harm to the study participants. We will evaluate reports from participants or research personnel regarding pain, discomfort, or injury subsequent to participation in the study.

### 18 Consent Process

Describe the process and procedures process you will use to obtain consent. Include a description of:

- Who will be responsible for consenting participants?
- Where will the consent process take place?
- How will consent be obtained?
- If participants who do not speak English will be enrolled, describe the process to ensure that the oral and/or written information provided to those participants will be in that language. Indicate the language that will be used by those obtaining consent. Translated consent forms should be submitted after the English is approved.
- The research coordinator or a designated staff member will be responsible for obtaining written informed consent (permission from parents) and assent from participants at ASU.
- All procedures will be explained to families in person in detail (their preferred language of English or Spanish). Any questions will be addressed. Special care will be taken to explain the assent document in detail to youth to ensure comprehension. Youth will be asked to explain back to research team what the study is about and what is involved to ensure appropriate explanations. Consents will be available in English and Spanish and the research team is comprised of several bilingual/bicultural members with extensive experience working with the Latino community. After the study team has explained the purpose and procedures verbally, participants will be asked to provide the team with a brief overview of the study to ensure comprehension. Questions may include: "Can you tell me why we are doing this study? Can you tell me one of the risks? Can you tell me one of the benefits?"

### 19 Investigational New Drug or Devices

If the drug is investigational (has an IND) or the device has an IDE or a claim of abbreviated IDE (non-significant risk device), include the following information:

- Identify the hold of the IND/IDE/Abbreviated IDE.
- Explain procedures followed to comply with FDA sponsor requirements for the following:

| FDA Regulation | Applicable to: |             |                         |
|----------------|----------------|-------------|-------------------------|
|                | IND Studies    | IDE studies | Abbreviated IDE studies |
| 21 CFR 11      | X              | X           |                         |
| 21 CFR 54      | X              | X           |                         |
| 21 CFR 210     | X              |             |                         |
| 21 CFR 211     | X              |             |                         |
| 21 CFR 312     | X              |             |                         |
| 21 CFR 812     |                | X           | X                       |
| 21 CFR 820     |                | X           |                         |

N/A

